**Visit 3A- Subject will return to clinic the next day, if in pK sub-study**
- ⊙ T= 24 hr pK draw, if applicable

### 5.3.3 Laboratory Procedures

- ⊙ Safety labs as defined in section 5.1.3
- ⊙ STD screen as defined in section 5.1.3
- ⊙ Research panel
  - Epithelial sloughing assay (Lavage)
  - Histopathology (~1 biopsy)
  - Mucosal mononuclear cell phenotype (~4 biopsies)
  - Mucosal cytokine profile (~3 biopsies)
  - Pre- and post-dose Immunoglobulin assay (~4 rectal sponges)
  - Fecal calprotectin assay (Stool)
  - Explants studies (~6 biopsies, ~10ml blood)
  - UC-781 blood level for sub-study participants (~25ml blood)

## 5.4 Treatment Stage 1- Follow-up Period

- ⊙ For a full 7 days after the flexible sigmoidoscopy subjects must refrain from insertion of anything per rectum.
- ⊙ An attempt will be made to contact the subject approximately one day after Visit 3 for a safety follow-up phone call. Potential AEs that arise may require further clinical evaluation.

## 5.5 Visit 4- (Week 5 +/- 2 weeks) Treatment Stage 2 Clearance

### 5.5.1 Non-clinical Procedures

- If subject had a positive STI result at Visit 3, the subject will be referred for treatment of that STI. The subject may proceed to (Visit 4) one week after a CDC-approved (Appendix X) treatment for the STI.
- Update locator information and remind participant that he or she will receive visit reminders via email and/or telephone.
- Collect copy of concomitant medication log
- Review precautions listed in Section 5.1.1.
- At this time subjects will be given clearance, if applicable, to start the once daily rectal administration of study product the next day and reminded to complete Product Use Log during Treatment Stage 2.
- Give participant Product Use Log, with instructions for proper use.
- Dispense study product and lubricant with thorough instructions for proper use. Instruction will include self-insertion of an empty applicator while a staff member is available to provide guidance.

### 5.5.2 Clinical Procedures

- Interval medical history\*, including AE assessment, will be collected to assure continued healthy status and safety of study interventions.  
\* Note for female participants this includes notation of the LMP.
- Basic physical examination as defined in section 5.1.2
- (If participant has peri-anal or rectal HSV lesions, referrals for treatment will be provided and Visit 3 will be postponed until outbreak resolved.)
- **If female of child-bearing potential, send STAT HCG testing**
- Collect blood, rectal swab specimens, and urine if applicable

### 5.5.3 Laboratory Procedures

- Qualitative HCG
- STD screen as defined in section 5.1.3

## 5.6 Treatment Stage 2- Outpatient

### Up to 3 weeks after Visit 3:

- Subjects may not begin study product administration, until they have been given clearance by the staff pending clinical labs.  
*If any lab abnormalities  $\geq$  Grade 2 at Visit 3, subject may not proceed with Treatment Stage 2. If the investigator feels that the laboratory abnormalities are transient, the lab tests may be repeated within the visit window. If the repeated labs tests are within normal limits, the subject may proceed with Treatment Stage 2 at the discretion of the investigator, the DAIDS Medical Officer, the SMC, and the IRB.*
- On approximately Day 4 of Treatment Stage 2, an attempt to contact the subject for an interim follow-up phone-call to assess safety, adherence, and troubleshoot any difficulties with administration will be made. Potential AEs that arise may require further clinical evaluation. At this time subjects will also be reminded to complete Product Use Log.

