### 5.3.2 Clinical Procedures

**NOTE: During this visit the timepoints listed below are approximate. Every effort will be made to adhere to the timeline, however due to logistics timing will not be exact. However, the sequence of sample collection during the following visits is crucial.**

- ⊙ Interval medical history\*, including AE assessment, will be collected to assure continued healthy status and safety of study interventions.
 

*\* Note for female participants this includes notation of the LMP.*
- ⊙ Basic physical examination as defined in section 5.1.2
 

*(If participant has peri-anal or rectal HSV lesions, referrals for treatment will be provided and Visit 3 will be postponed until outbreak resolved.)*
- ⊙ **If female of child-bearing potential, collect urine for STAT HCG testing**
- ⊙ Collect blood specimens, including pre-dose pK draw if applicable
- ⊙ Collect rectal swabs and sponge specimens

- ⊙ Administer preparatory Normosol-R pH7.4 enema
- ⊙ Collect stool specimen
- ⊙ T=0 Administration of single-dose of study gel by study staff  

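### The laboratory gate to Treatment Stage 2 appears to rest on blood drawn before the first dose, so no blood count or metabolic panel is scheduled between that dose and Visit 5

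*Protocol*

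**What the plan says.** **Visit 3 (Sections 5.3.2 and 5.3.3).** The clinical procedures are an ordered list. Times are approximate, but "the sequence of sample collection during the following visits is crucial". The general blood item is "Collect blood specimens, including pre-dose pK draw if applicable". It comes before the enema and before "T=0 Administration of single-dose of study gel by study staff". After the dose, the only blood listed is for pharmacokinetics, at 15 minutes, 2 hours, 4 hours and 24 hours, and only for sub-study participants. The laboratory list includes "Safety labs as defined in section 5.1.3", which means a complete blood count, a metabolic panel with magnesium, and HCG where relevant.

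**After Visit 3 (Section 5.4).** "An attempt will be made to contact the subject approximately one day after Visit 3 for a safety follow-up phone call".

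**Visit 4 (Sections 5.5.1 to 5.5.3).** This is the Stage 2 clearance visit. It includes an interval history with adverse event assessment, a physical examination (which includes anoscopy under Section 5.1.2), and the item "Collect blood, rectal swab specimens, and urine if applicable". The laboratory list has two entries, HCG and the STD screen. Cleared participants are allowed "to start the once daily rectal administration of study product the next day".

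**Gate to Stage 2 (Section 5.6).** With an abnormality at or above "Grade 2 at Visit 3, subject may not proceed with Treatment Stage 2". Tests may be repeated only when the Visit 3 result is abnormal and thought transient.

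**Visit 5 (Sections 5.7 and 5.7.3).** Safety labs are next scheduled here, on Day 8 of Stage 2 (+/- 1 day).

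**The concern.** The protocol chose to put a laboratory check between the single dose and the seven-day course. Such a check can only screen for an effect of the single dose if the sample follows that dose. Sections 5.2.1 and 5.3.1 use the same rule, in which the previous visit's labs clear the next step. There it works, because no study gel has been given between sample and step. Section 5.6 is the only place where a dose falls in between.

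Two things are at stake. The first is participant safety: Section 8.3 says that this formulation had not been given rectally to humans, yet seven more doses are cleared without a scheduled look at haematology or chemistry after the first. The second is attribution. Section 2.2 declares the two stages independent and aims to describe two regimens, not their cumulative toxicity. Grade 2 or higher adverse events are the primary safety measure (Section 7.4), and graded laboratory changes count among them. A laboratory event first found at Visit 5 could come from either stage.

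**Working it through.** **1. Order of events.**

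| Step | Source | Blood count or metabolic panel? |
|---|---|---|
| Visit 1 | 5.1.3 | Yes, before any dose |
| Visit 2 | 5.2.3 | Yes, before any dose |
| Visit 3, general draw | 5.3.2, 5.3.3 | Yes, listed before T=0 |
| Visit 3 dose | 5.3.2 | Dose 1 |
| 15 min, 2 h, 4 h, 24 h | 5.3.2 | No; pharmacokinetic draws, sub-study only |
| Visit 4 | 5.5.3 | No; HCG and STD screen |
| Stage 2 | 4.4, 5.6 | Doses 2 to 8 |
| Visit 5 | 5.7.3 | Yes |

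Of 4 scheduled panels, 1 appears to follow a dose. It comes after 1 + 7 = 8 doses.

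**2. Is the Visit 3 tube really pre-dose?** The text does not say so outright; two observations support it.
- The sub-study has 9 of 36 participants. For the other 36 - 9 = 27, no post-dose blood is listed at Visit 3, so the listed pre-dose draw is the only place for the safety tube.
- Within the sub-study, Visits 3 and 3A have 5 draws (pre-dose, 0.25, 2, 4 and 24 hours). One draw is about 5 ml (the Visit 5 volume in Section 5.7.3), and 5 x 5 = 25 ml. Section 5.3.3 states about 25 ml, so the pharmacokinetic volume has no room for a safety tube.

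**3. Time from first dose to first post-dose panel.** Assume that Stage 2 Day 1 is day 8 after Visit 3 at the earliest (after the full 7-day recovery) and day 21 at the latest (the 3-week limit). Visit 5 is Stage 2 Day 8, which is 7 days after Day 1.
- Earliest: 8 + 7 = day 15.
- Latest: 21 + 7 = day 28.
- Each is +/- 1 day. The nominal visit weeks (Visit 3 at week 2, Visit 5 at week 6) give 4 weeks, the upper end.

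**4. What a Visit 4 panel would gain in time.** Section 2.2 places Visit 4 in the week before Stage 2, so 1 to 7 days before Day 1. Visit 5 is 7 days after Day 1. The gap is 1 + 7 = 8 to 7 + 7 = 14 days.

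**5. The plan's own probabilities.** Section 7.4 gives more than 90% and 11% for at least one event in 12 subjects at true rates of 20% and 1%. Both reproduce: 1 - 0.80^12 = 0.931 and 1 - 0.99^12 = 0.114. They are illustrations for adverse events of any kind. The documents give no rate for laboratory events after one dose, and no share still present at Visit 4. Purely as an illustration at the 1% rate, a Visit 4 panel would show at least one such event in an arm of 12 with probability 1 - (1 - 0.01f)^12. This is 3%, 6% and 11% for assumed persistence shares f of 25%, 50% and 100%. The point does not depend on these figures.

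**The case against.** The strongest reply is that this is a deliberate and consistent design. Sections 5.5.3 and 5.6 agree with each other, and post-dose checks do exist before Stage 2: the next-day call, and the Visit 4 history and examination with anoscopy. Unscheduled work-up is available, and the SMC can be convened at any time (Section 6.1). The dose is small: 3.5 g of 0.25% gel holds 8.75 mg of UC-781. Six vaginal doses at 0.1% and 0.25% gave no detectable plasma level. Macaques given four rectal doses of up to 1.0% gel had none in serum. Rabbits given rectal gel up to 2.5% showed no systemic toxicity, with the final report pending. All of this stands and limits the weight of the point. It leaves open only symptomless haematology or chemistry changes, which are what a laboratory gate is for.

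It is also fair that the timing is inferred. Section 5 refers to Appendix I for the visit schedule and to a procedures manual for detail; neither was available. But if the safety tube were taken after the dose at Visit 3, it would be drawn within hours of dosing and would show little of its effect. A note to that effect would not repair the gate.

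Some stronger readings are tempting and are not supported:
- That participants enter Stage 2 with no safety review. The clinical checks above contradict this.
- That the comparison with placebo is biased. All arms follow the same schedule.
- That a Visit 4 panel would very probably catch an event. This would treat the 20% example in Section 7.4 as a laboratory event rate after one dose, which the documents do not say, and the absorption data point the other way.

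**Conclusion.** The point holds as a gap in the schedule and should be fixed. As the procedures are listed, the Stage 2 laboratory gate looks at a sample that precedes the dose it should screen, and no blood count or metabolic panel is scheduled from the first dose until Visit 5, 8 doses and about 15 to 28 days (+/- 1) later. A persistent change may still be found at Visit 5, but later and without a stage to assign it to. Confidence is moderate, because the conclusion rests on list order and blood volumes, not on an explicit statement. The day counts also assume that Stage 2 starts between day 8 and day 21. The consequence is limited to laboratory safety within participants and to attribution between the two regimens, and the expected number of such events is low.

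**What to change.** - **Section 5.5.3:** add the Section 5.1.3 blood count and metabolic panel to the Visit 4 draw.
- **Section 5.6:** base the Stage 2 clearance, and the rule on repeat tests, on the Visit 4 result. Whether the Grade 2 threshold should carry over unchanged is for the clinical team.
- **Section 5.5.1:** replace the next-day start with a start once results are available. Section 2.2 already allows up to a week between Visit 4 and Stage 2, and Section 5.6 already forbids dosing before clearance.

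The Visit 3 panel then serves as the pre-dose reference, and the Visit 4 panel gives a reading for Stage 1 alone, about 8 to 14 days before Visit 5. If the change is not made, Section 7.4 should say that laboratory events first seen at Visit 5 may reflect either stage.

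The cost is about 10 ml more blood at an existing venepuncture for up to 36 participants and a short wait for results. The amendment is short but needs the approvals in Section 10.4. No visit or procedure is added. A change that resolves before Visit 4 would still be missed.

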## 5.7 Visit 5 – (Week 6 +/- 2 weeks) Treatment 2 Follow-up

*Although time from Week 0 may vary by several weeks, visit must be scheduled for Day 8 of Treatment Stage 2 (the day following the last dose of study product +/- 1 day).*

### 5.7.1 Non-clinical Procedures

- ⊙ Update locator information and remind participant that he or she will be contacted to complete an in-depth acceptability interview.
- ⊙ Collect Product Use Log and unused product.
- ⊙ Collect copy of concomitant medication log
- ⊙ Review precautions listed in Section 5.1.1.
- ⊙ Review instructions for use of CASI to complete Product Acceptability Questionnaire (PAQ).

### 5.7.2 Clinical Procedures

- ⊙ Interval medical history\*, including AE assessment.  
*\* Note for female participants this includes notation of the LMP.*
- ⊙ Basic physical examination as defined in section 5.1.2  
*(If participant has positive STI test result and/or peri-anal or rectal HSV lesions, Visit 5 will still be performed for safety evaluation. Every effort will be made to ensure the comfort of the participant make appropriate referrals for treatment.)*
- ⊙ Collect blood and rectal swab specimens
- ⊙ Collect rectal sponge specimens
- ⊙ Administer preparatory Normosol-R pH7.4 enema
- ⊙ Collect stool specimen
- ⊙ Perform flexible sigmoidoscopy, including:
  - Rectal lavage at approximately 5cm
  - 14 biopsies at approximately 10cm
  - 14 biopsies at approximately 30cm
  - \* each biopsy measures 8 mm x 2 mm x 1 mm*

### 5.7.3 Laboratory Procedures

- ⊙ Safety Labs as defined in section 5.1.3
- ⊙ STD screen as defined in section 5.1.3
- ⊙ Research panel
  - Epithelial sloughing assay (Lavage)
  - Histopathology (~1 biopsy)
  - Microflora (~1 rectal swab)
  - Mucosal mononuclear cell phenotype (~4 biopsies)
  - Mucosal cytokine profile (~3 biopsies)
  - Immunoglobulin assay (~ 2 rectal sponges)
  - Fecal calprotectin assay (Stool)
  - Explants studies (~6 biopsies, ~10ml blood)
  - UC-781 blood level for sub-study participants (~5ml)

## 5.8 Treatment Stage 2- Follow-up Period

- ⊙ For a full 7 days after the flexible sigmoidoscopy subjects must refrain from insertion of anything per rectum.
- ⊙ An attempt will be made to contact the subject for a safety follow-up phone call approximately one day after Visit 5. Potential AEs that arise may require further clinical evaluation.

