After completion of Visit 5, subjects will be contacted by an interviewer to complete an in-depth phone interview regarding product acceptability. [The complete results of these interviews will not be shared with the rest of the research staff until the blind has been broken, as subjects may unwittingly reveal information that would break the blind. Only preliminary data that does not compromise the blind may be shared prior to data lockdown and unblinding.]

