**Table 3: Product Acceptability Questionnaire (See Appendices VI a and VI b)**

| Section | Title:                                 | Content                                                                                                                                                                                         |
|---------|----------------------------------------|-------------------------------------------------------------------------------------------------------------------------------------------------------------------------------------------------|
| A       | PRODUCT ACCEPTABILITY                  | Likes and dislikes of physical characteristics of the product and sensations                                                                                                                    |
| B       | APPLICATION PROCESS                    | Ease of application, position, timing                                                                                                                                                           |
| C       | APPLICATOR                             | Likes and dislikes about applicator, its tip, and its portability                                                                                                                               |
| D       | CHANGES IN VOLUME USED                 | Any changes introduced by the user in the volume of product applied                                                                                                                             |
| E       | EXPERIENCES USING THE PRODUCT          | Leakage, soiling, or other product side effects, and how much the participant was bothered by them; feeling that the product was absorbed in the intestine                                      |
| J       | INTENTION TO USE PRODUCT IN THE FUTURE | Willingness to use a product that contributed to provide some protection against HIV; willingness to use it when condoms are not used, if wait period were required, and according to its cost. |
| K       | WILLINGNESS TO USE HIGHER VOLUME       | Attitudes about different product volumes                                                                                                                                                       |

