### 5.9 Visit 6- (within 2 weeks of visit 5) In-depth Telephone Interview

Study staff will contact subject to conduct in-depth acceptability interview via telephone (see script in Appendix VI). Interviewers will use a basic script to initiate discussion, but interviews will vary according to participant responses.

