#### Pregnancy

*Pregnancy will not be considered an Adverse Event for this study. Pregnancy will require the subject to be withdrawn from the study. However, in the event that a subject becomes pregnant during the study every reasonable effort will be made to follow her through pregnancy outcome. Consent for the site to receive a copy of her medical records related to the pregnancy should be obtained.*

*Anytime a live birth pregnancy is reported, an attempt to collect medical records of the neonate should be made.*

Study site staff will document on study CRFs all AEs reported by or observed in enrolled study participants regardless of severity and presumed relationship to the study product and procedures.

Information on all AEs will be included in reports to the US Food and Drug Administration (FDA), and other applicable government and regulatory authorities. Site staff will report information on all AEs and EAEs to their Institutional Review Board (IRB) in accordance with all applicable regulations and local IRB requirements.

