#### **RISKS FROM FLEXIBLE SIGMOIDOSCOPY WITH BIOPSIES**

Flexible sigmoidoscopy is a commonly practiced medical procedure and the endoscopic procedures done in this trial will not involve any unusual risks or discomforts. The risks associated with these procedures include mild discomfort and the feeling of having a "bloated stomach". Endoscopic biopsies are painless and heal quickly within 3 days. On extremely rare occasions, the endoscopic procedure or biopsies may lead to pain, infection (sepsis), bleeding or perforation of the gastrointestinal tract. Perforation occurs approximately once out of every 100,000 procedures. If this extremely rare complication occurs, antibiotics and surgery to repair the tear may be necessary. The impact of the rectal application of UC-781 on the intestinal mucosa is unknown and may increase the risk of these complications.

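### After the attempted call one day after Visit 5, adverse events in Stage 2 are captured only by self-report, and no route is stated for an event mentioned at Visit 6

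*Protocol*

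**What the plan says.** **End of Stage 2.** Protocol section 5.7 fixes the timing of Visit 5: "visit must be scheduled for Day 8 of Treatment Stage 2 (the day following the last dose of study product +/- 1 day". Section 5.7.2 lists an interval history with AE assessment and an examination, then sigmoidoscopy with 14 biopsies at each of two sites. Section 5.8 follows with seven days of rectal rest and this contact: "An attempt will be made to contact the subject for a safety follow-up phone call approximately one day after Visit 5".

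**Later contact.** Section 5.9 is headed "Visit 6- (within 2 weeks of visit 5) In-depth Telephone Interview" and says: "Study staff will contact subject to conduct in-depth acceptability interview via telephone". It lists no AE assessment.

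**Embargo.** The Schema and section 2.2 both state: "The complete results of these interviews will not be shared with the rest of the research staff until the blind has been broken". The next sentence in each place allows preliminary data to be released earlier if they do not endanger the blind.

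**AE recording.** Section 6.3 requires: "Study site staff will document on study CRFs all AEs reported by or observed in enrolled study participants regardless of severity". It also gives participants a 24-hour number and tells them to report any event. Under section 6.4.1, expedited reporting runs to study completion.

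**Stage 1.** Section 5.4 has the same one-day call after Visit 3. Section 5.5.2 then adds an AE history and examination at Visit 4.

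**The concern.** The primary safety measure in section 7.4 is the frequency of Grade 2 or higher AEs, and the stated aim is to examine two dosing regimens. Section 8.3 says that this formulation has not been given rectally to humans before, and that its unknown effect on the mucosa may raise the risk of biopsy complications. The days after the Visit 5 biopsies, which follow the seven-day regimen, are therefore a period in which AEs should be asked about.

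As written, scheduled questioning ends with one attempted call. If that call fails, no AE question is scheduled after the biopsies at all. The one later conversation draws out a detailed account of using the gel, so symptoms may well be mentioned there. Its full results are held until the blind is broken, which under section 7.3 follows data lock. Nothing tells the interviewer what to do with an AE. An event could be told to a member of the study team and still reach the clinician, the CRF and the Grade 3 trigger in section 6.1 late.

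**Working it through.** **Timeline of scheduled AE questions**

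- Last Stage 2 dose: Day 7. Visit 5: Day 8, with a window of one day either side. Call: about one day later, so Day 9 (Day 8 to Day 10).
- From last dose to call: 9 − 7 = 2 days (range 1 to 3).
- From biopsies (14 + 14 = 28) to call: about 1 day.
- Section 8.3 on healing: "Endoscopic biopsies are painless and heal quickly within 3 days". Healing time left after the call: 3 − 1 = 2 days.
- Rectal rest left after the call (section 5.8): 7 − 1 = 6 days.
- Visit 6 is at most 14 days after Visit 5, so the longest gap after the call is 14 − 1 = 13 days. This is a maximum; an early Visit 6 shortens it.

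**The two stages side by side, after the sigmoidoscopy**

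| | Stage 1 | Stage 2 |
|---|---|---|
| Attempted safety call | about 1 day | about 1 day |
| Later AE history and examination | Visit 4, nominally Week 5 − Week 2 = 3 weeks after Visit 3 | none listed |
| Later contact of any kind | Visit 4 | Visit 6, acceptability interview only |

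The windows for Visits 3 and 4 are wide, so the Stage 1 interval can be shorter than three weeks. The 7-day recovery period sets a floor of about a week if dosing starts the day after Visit 4, as section 5.5.1 describes.

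**Embargo against recording duty**

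Section 6.3 obliges site staff to record every AE reported to them. The Schema and section 2.2 hold back the complete interview results and permit, but do not require, release of preliminary data that leave the blind intact. Neither passage mentions safety information, a recipient or a time limit. The two provisions can coexist, but the step that joins them is not written.

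**The plan's own detection figures**

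Section 7.4 gives the chance of at least one AE in 12 subjects. The formula is 1 − (1 − p)^12.

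- p = 0.20: 1 − 0.80^12 = 93.1% (plan: more than 90%). Reproduced.
- p = 0.01: 1 − 0.99^12 = 11.4% (plan: 11%). Reproduced.

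**Illustration of sensitivity to missed events**

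Assume that a share q of affected subjects have their only event after the call and that it is never recorded. The documents give no value for q. At a true rate of 20%, the chance of recording at least one event is 1 − (1 − 0.20 × (1 − q))^12:

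| q | Recorded rate | Chance of at least one in 12 |
|---|---|---|
| 0 | 0.20 | 93.1% |
| 10% | 0.18 | 90.8% |
| 25% | 0.15 | 85.8% |
| 50% | 0.10 | 71.8% |

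The 90% level needs a recorded rate of 1 − 0.1^(1/12) = 0.1746, so it is lost once q exceeds 1 − 0.1746/0.20 = 12.7%. This shows how the stated figure responds. It does not estimate the loss.

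**The case against.** The strongest reply is that AE capture does not stop with the call. Participants can use the 24-hour line, site staff must record what they hear, and expedited reporting runs to study completion. Stage 2 also has active surveillance during exposure: a call on about Day 4, then history, examination, safety laboratory tests and sigmoidoscopy at Visit 5. The length of post-treatment contact is a design choice. All of this stands. Late events are not outside safety monitoring; their capture depends on the participant volunteering them, or on an interviewer passing them on without a stated instruction.

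Four stronger readings are tempting, and the documents do not support them.

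- *The embargo blocks all AE information.* It covers complete results and expressly lets non-unblinding data through. It does not lift the duty in section 6.3.
- *Side effects entered in the Product Acceptability Questionnaire (PAQ) are withheld too.* Section E of the PAQ does ask about "Leakage, soiling, or other product side effects, and how much the participant was bothered by them". But the embargo names only the interviews, and the questionnaire is completed in the Visit 5 window, so it says little about delayed events.
- *The schedule favours a clean result for the seven-day regimen.* All three arms share one schedule, the primary comparison is with placebo, and section 7.4 plans no test of one stage against the other. No bias between arms is shown.
- *The call catches only a fixed fraction of post-procedure events, such as one day in seven.* The seven days are an abstinence rule, not a risk window, and no late-event rate is given.

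The Appendix I schedule, the Appendix VI interview script and the study-specific procedures manual are not in the text at hand. An AE prompt or hand-over rule there cannot be excluded. If one exists, section 5.9 and the embargo text should refer to it.

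**Conclusion.** The point holds as a gap in scheduled ascertainment and in the stated flow of safety information. Active AE questioning after Stage 2 ends about two days after the last dose and one day after 28 biopsies, up to 13 days before the final contact. It ends before the protocol's own healing and rest periods do, and it lacks the later check that Stage 1 receives. The effect is reduced sensitivity of the primary safety measure for the repeated-dose regimen, equally in every arm. How much is lost cannot be established from the documents, since it depends on the rate of late events and on how often participants report them unprompted. The conclusion assumes that the visit content in sections 5.7 to 5.9 is complete as written. It is worth correcting before enrolment because the remedy is cheap and this is the first rectal use of the formulation in humans.

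**What to change.** - **Section 5.9:** add a short AE and concomitant-medication check at the Visit 6 contact, done by site staff and kept separate from the acceptability interview.
- **Schema and section 2.2:** state that safety information is exempt from the embargo. Any AE mentioned to the interviewer goes promptly to the study clinician as event, date and severity only, and is entered on the CRF under section 6.3.

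The cost is a minor amendment and a few minutes of staff time on a contact already scheduled. The downside is a small risk of a remark that reveals the blind, limited by passing on only those three items. No dose, visit window or clinical rule changes.
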